### Testing and Validation

To facilitate decision making on the optimal analytic approach, three steps will be undertaken: (1) develop the correct model for each algorithm using the training dataset, (2) apply the final model for each algorithm on the test dataset, and (3) apply the best performing algorithm on the validation dataset.

In Step 1, algorithms will be run using the training dataset comprising 60% of the total sample from across all states for which data are available. For each algorithm, iterative testing will be run to select the best model that fits the data. The emerging results will then be assessed for model fit and accuracy. Table 4 summarizes the four proposed metrics for assessing the performance of each model.

**Table 3 table3:** Performance comparisons of learning algorithms modified from Kotisiantis et al [17,18] (++++ represents the best and + the worst performance).

Model attributes	Decision trees	NNs	Naïve Bayes	SVM	Linear discriminant analysis	Logistic regression
Accuracy in general	++	+++	+	++++	+++	++
Speed of learning with respect to number of attributes and number of instances	+++	+	+++	+		
Speed of classification	++++	++++	++++	++++	++++	++
Tolerance to missing values	+++	+	++++	++	+++	+
Tolerance to irrelevant attribute	+++	+	++	++++	+++	+
Tolerance to redundant attributes	++	++	+	+++	++	+
Tolerance to highly interdependent attributes	++	+++	+	+++	++	+
Dealing with discrete/ binary/ continuous attributes	++++	+++ (not discrete)	+++ (not continuous)	+++ (not discrete)	++++	+++
Tolerance to noise	++	++	+++	++	+++	++
Dealing with danger of overfitting	++	+	+++	++	++	+
Attempts for incremental learning	++	+++	++++	++		
Explanation ability/ transparency of knowledge/ classification	++++	+	++++	+	+	+
Model parameter handing	+++	+	++++	+	++	+

**Table 4 table4:** Metrics for assessing the performance of each model.

Model metrics	Formula^a^	Description
Accuracy	(TP+TN)/(TP+TN+FN)	Proportion of cases correctly classified
Precision or positive predictive value	TP/(TP+FP)	Fraction of relevant instances among the retrieved instances
Sensitivity or recall	TP/(TP+FN)	Fraction of relevant instances retrieved over total amount of relevant instances
Area under receiver operating characteristic curve (AUROC)	Area covered by the function of true positive rate/ false positive rate	The curve is plotted and area between the curve and the 45° line is multiplied by 2 to give the AUROC. A value of 1 represents perfect accuracy while 0.5 means the prediction is worthless.

^a^TP: true positive, TN: true negative, FP: false positive, FN: false negative

To illustrate the definition of performance metrics for Mobile Academy, we define true positives (TP) as the number of correctly classified ASHAs who have completed the training, and true negatives (TN) as the number of correctly classified ASHAs who have not completed the training. False positives (FP) are defined as the number of ASHAs incorrectly classified as having completed the training, while false negatives (FN) are the number of ASHAs incorrectly classified as not having completed the training.

Results from the performance metrics will help define the final model for each algorithm. In Step 2, these final models for each algorithm will be applied to the test dataset, which comprises approximately 20% of the total data. Using the same performance metrics, the models with the best fit and accuracy will be applied to the validation dataset as part of Step 3. Ultimately, predictions for Mobile Academy will aim to determine the probability of the ASHA finishing the course in a predetermined time frame and the possible score/performance of the individual ASHAs. For Kilkari, we will determine predictors for exposure to Kilkari content based on user characteristics, as well as explore the effect of early listening patterns on postpartum engagement and overall exposure.

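### Table 4's doubling rule for the AUROC gives the Gini index (2×AUROC − 1), which contradicts the same row's formula and its 0.5 benchmark

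*Protocol article*

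**What the plan says.** The Testing and Validation section of the protocol article introduces its performance measures with the statement "Table 4 summarizes the four proposed metrics for assessing the performance of each model". The AUROC is the fourth row of that table, and the row makes three statements about it.

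- The Formula column reads "Area covered by the function of true positive rate/ false positive rate".
- The Description column gives a way to obtain the number: "The curve is plotted and area between the curve and the 45° line is multiplied by 2 to give the AUROC".
- The Description column then gives the scale on which to read it: "A value of 1 represents perfect accuracy while 0.5 means the prediction is worthless".

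On how the metrics are used, the text after the table says "Results from the performance metrics will help define the final model for each algorithm". The same metrics are applied again on the test set to decide what goes forward to the validation set. The Training of Algorithms section separately says that the preferred approach is the one with the smallest total classification error.

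**The concern.** The computing rule and the reading scale sit side by side in one cell, and they belong to two different statistics. A value computed by the rule and read on the scale would be misinterpreted: a chance-level model would score 0 where the cell says 0.5, and a model with moderate discrimination could score at or below the value that the cell calls worthless. Figures produced this way would also not be comparable with AUROCs published elsewhere.

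The readership makes the error less harmless than it would be in a technical paper. The Introduction addresses practitioners without a machine learning background, and the Discussion hopes that similar messaging programs may take up the approaches. Such readers are the least likely to notice the slip.

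**Working it through.** **Inputs.** All come from the AUROC row of Table 4: the computing rule (twice the area between the ROC curve and the diagonal), the two anchors (1 for perfect, 0.5 for worthless), and the Formula column (area under the curve of true positive rate against false positive rate, loosely worded). No sample size, error rate or effect size enters.

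**Step 1: what the rule computes.** Let A be the whole area under the ROC curve in the unit square. The diagonal cuts the square in half, so the area under it is 0.5. The area between curve and diagonal is therefore A − 0.5, and the rule gives

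2 × (A − 0.5) = 2A − 1.

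This is the Gini index, also known as Somers' D.

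**Step 2: try to reproduce the stated anchors.**

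| Definition | Chance (A = 0.5) | Perfect (A = 1) | Matches 0.5 and 1? |
|---|---|---|---|
| Doubling rule, 2A − 1 | 2 × 0.5 − 1 = 0 | 2 × 1 − 1 = 1 | No: chance is 0 |
| Whole area, A | 0.5 | 1 | Yes |
| 0.5 plus area between curve and diagonal | 0.5 + 0 = 0.5 | 0.5 + 0.5 = 1 | Yes (identical to A) |

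The doubling rule meets the upper anchor but not the lower one. The ordinary area, which is what the Formula column points to, meets both.

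**Step 3: size of the mis-scaling if the rule is applied literally.**

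| True AUROC | Value by the rule (2A − 1) |
|---|---|
| 0.50 | 0.00 |
| 0.60 | 0.20 |
| 0.70 | 0.40 |
| 0.75 | 0.50 |
| 0.80 | 0.60 |
| 0.90 | 0.80 |
| 1.00 | 1.00 |

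Numerical integration of binormal ROC curves with A from 0.5 to 1.0 gave the same values. Solving 2A − 1 = 0.5 gives A = 0.75, so a model with a true AUROC of 0.75 would carry the number that the cell labels worthless, and models between 0.50 and 0.75 would carry smaller ones.

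**Step 4: effect on comparing models.** 2A − 1 rises strictly with A. If one model has the larger AUROC, it also has the larger doubled area, so their order on this metric is the same on either scale. Only the spacing changes: gaps are doubled, so that 0.70 against 0.75 appears as 0.40 against 0.50.

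**The case against.** The strongest reply is that this is one bad sentence in an otherwise correct row. The metric is named as the area under the curve, the Formula column describes that area, and both anchors are right for it. The sentence is part of a lay explanation; nothing says that analysts will work out the metric by hand in this way, and standard software would normally return the ordinary AUROC. Model choice is comparative, and the ranking on this metric is unaffected. The AUROC is also only one of four metrics that help to define the final model, alongside the stated aim of minimizing total classification error.

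All of that stands, and it limits the consequence. In particular, a reader might infer that useful models would be declared worthless and dropped. The article does not support this. It sets no AUROC threshold for accepting, rejecting or labelling a model; the 0.5 is an explanatory anchor for chance, and treating every value at or below it as worthless goes beyond the text.

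The reply does not remove the contradiction. The sentence says how the number is obtained, it is wrong for the metric it names, and it conflicts with the sentence after it. A lay setting is no defence when the purpose of the article is to explain the method. Nor is this detail that a condensed article leaves to a fuller document: the definition is stated, and stated wrongly.

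**Conclusion.** The concern holds as a definitional error. Twice the area between the ROC curve and the diagonal is 2×AUROC − 1, not the AUROC, and it is incompatible with the 0.5 anchor and with the Formula column of the same row. The possible harm is to reported values and how they are read: the rule understates the AUROC by 1 − A, that is, by 0.50 at chance, 0.25 at a true AUROC of 0.75 and 0.10 at 0.90. It does not reach the choice of model through this metric.

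The size rests on two assumptions: that the sentence is applied literally rather than bypassed by software, and that the area is taken as signed, so that a curve below the diagonal counts as negative. The contradiction in the text depends on neither. The severity is a minor correction.

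**What to change.** Replace the doubling sentence in Table 4. State that the AUROC is the whole area under the curve of true positive rate plotted against false positive rate, or equivalently 0.5 plus the area between the curve and the diagonal, with 1 for perfect discrimination and 0.5 for chance. It would help to reword the Formula column in the same terms, since its slash can be read as a ratio of the two rates.

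If the doubled area is what the authors want, name it the Gini index, give 2×AUROC − 1 as its formula, and set chance at 0.

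Whichever is chosen, results should state which of the two is reported, so that values can be set against other studies. The cost is one table row in the text, with no new data and no extra analysis.

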Study aims.Aim 1: Describe subscriber losses at different points during pregnancy and postpartum period from the programObjective 1a. Determine differences in subscribers who remain subscribed to Kilkari throughout the duration of service versus those lost at different points along the continuum of program databases.Objective 1b. Develop a classifier for identifying different categories of losses.Aim 2: Facilitate the program’s ability to identify and target ASHAs likely to perform poorly on digital health training programs and knowledge assessmentsObjective 2a. Determine predictors of training course completion (overall and time to completion) by ASHAs based on performance on early modules of the course and other characteristics including reported motivation, knowledge, individual characteristics, and mobile literacy.Objective 2b. Develop a classifier for the routine identification of ASHAs likely to perform poorly.Aim 3: Understand the factors underpinning successful receipt of calls (are calls received?)Objective 3a. Determine what proportion of calls successfully reach the end-user’s device for Kilkari.Objective 3b. Identify the proportion of content specific to infant feeding and family planning received by end-users for Kilkari.Aim 4. Determine how users are listening to messagesObjective 4a. Determine predictors for exposure to Kilkari content based on user characteristics.Objective 4b. Measure exposure to Kilkari content based on technological and behavioral (end-user engagement) performance.Objective 4c. Develop a classifier for measuring listening levels.Aim 5: Understand optimal message delivery options for maximal impactObjective 5a. Determine message delivery options with the most success in engaging client and assess patterns of listening.Objective 5b. Determine the effect of early listening patterns (time of day of listening, duration and frequency of listening, content listening patterns) on postpartum engagement and overall exposure.

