### Training of Algorithms

Once data have been processed, testing of algorithms will be carried out. Table 2 summarizes the algorithms proposed for training along with their intended applications to Mobile Academy and Kilkari. To determine the model with the best fit, we will explore several machine learning approaches in turn. Models will be fit on the training set, and the fitted model used to predict the responses for the observations in the validation set. The preferred analytic approaches will be selected based on their ability to minimize the total error of the classification, where the latter is defined as the probability that a solution will classify an object under the wrong category. We describe each approach considered below in lay terminology, along with indications for use, and its proposed application in the evaluations of Mobile Academy and Kilkari.

**Table 2 table2:** Summary of algorithms proposed for testing and their intended application to Mobile Academy and Kilkari.

Algorithm		Description	Intended evaluation application	
			Mobile Academy	Kilkari

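### Selecting models on unweighted total error suits Objective 2b poorly: if most ASHAs complete the course, it favours models that flag few or no poor performers

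*Protocol article*

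**What the plan says.** Three parts of the Protocol article bear on this point.

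- **Purpose.** Textbox 1 in the Introduction gives Objective 2b as: "Develop a classifier for the routine identification of ASHAs likely to perform poorly".
- **Selection.** The section Training of Algorithms states: "The preferred analytic approaches will be selected based on their ability to minimize the total error of the classification". It defines that error as the probability of putting an object in the wrong category, with no weighting by class. Testing and Validation adds that, after the test set, "the models with the best fit and accuracy will be applied to the validation dataset as part of Step 3".
- **Metrics.** Table 4 lists accuracy, precision, sensitivity and AUROC. The worked illustration for Mobile Academy takes the completer as positive: "we define true positives (TP) as the number of correctly classified ASHAs who have completed the training". Its counterpart is "False positives (FP) are defined as the number of ASHAs incorrectly classified as having completed the training". Sensitivity is described as "Fraction of relevant instances retrieved over total amount of relevant instances". For AUROC the table says: "A value of 1 represents perfect accuracy while 0.5 means the prediction is worthless".

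The stated outputs for Mobile Academy are to "determine the probability of the ASHA finishing the course in a predetermined time frame" and to predict the ASHA's score or performance.

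**The concern.** The classifier in Objective 2b is a targeting tool. It is useful only if it finds the ASHAs who will do badly without flagging too many of the others. Two features of the plan work against that, and they are separate.

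1. **The selection rule.** Total error weighs a missed poor performer the same as a completer flagged by mistake. When poor performers are a minority, the cheapest way to lower total error is to flag few of them.
2. **The reporting.** With completers coded as positive, sensitivity is the share of completers found and precision is the share of predicted completers who are right. A missed non-completer is a false positive. Specificity, which under this coding is the recall of non-completers, is not in Table 4. Neither is negative predictive value, which would be the precision of a flag.

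Together they allow a model to be chosen and reported with high accuracy, sensitivity and precision although it finds few of the ASHAs it was built to find.

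**Working it through.** The document gives no completion rate and no performance figure, so there is nothing of its own to reproduce. The rates below are assumptions. Accuracy is taken as the proportion correctly classified, which is how Table 4 describes it. The printed accuracy formula omits false positives from its denominator; that is a separate matter, and nothing here relies on it.

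**Step 1. Flag nobody against a useful classifier.** Let p be the share of non-completers. The useful classifier is assumed to have sensitivity 0.70 and specificity 0.85 for non-completers.

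- Total error, flag nobody: p
- Total error, useful classifier: 0.30p + 0.15(1 − p)

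| Non-completion p | Flag nobody | Useful classifier | Lower total error |
|---|---|---|---|
| 5% | 5% | 1.5% + 14.25% = 15.75% | flag nobody |
| 10% | 10% | 3% + 13.5% = 16.5% | flag nobody |
| 20% | 20% | 6% + 12% = 18% | useful |
| 50% | 50% | 15% + 7.5% = 22.5% | useful |

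Break-even: p = 0.30p + 0.15(1 − p), so 0.85p = 0.15 and p = 17.6%. Below that rate flagging nobody wins; at every rate above it the useful classifier wins.

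**Step 2. Other comparators.** Let a be the sensitivity and b the specificity for non-completers. Flagging nobody wins when the completion share exceeds a/(a + 1 − b):

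- a = 0.70, b = 0.90: 0.70/0.80 = 87.5%
- a = 0.60, b = 0.85: 0.60/0.75 = 80%
- a = 0.70, b = 0.80: 0.70/0.90 = 77.8%

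**Step 3. What Table 4 would show.** At 10% non-completion, flagging nobody has sensitivity 1.00, precision 0.90 and accuracy 0.90 under the completer-positive coding. Its recall of non-completers is 0. Its AUROC is 0.50.

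**Step 4. A model that ranks well.** Suppose scores are normal with equal variance in the two groups and AUROC is 0.75. The separation is d = √2 × Φ⁻¹(0.75) = 0.954. Minimising total error with calibrated probabilities flags an ASHA only when her predicted risk exceeds 50%. On the score scale that cut-off is t = d/2 + ln[(1 − p)/p]/d, and the share of non-completers found is 1 − Φ(t − d).

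- p = 10%: t = 0.477 + 2.197/0.954 = 2.780; share found 1 − Φ(1.826) = 3%
- p = 20%: t = 1.930; share found 1 − Φ(0.976) = 16%
- p = 30%: t = 1.365; share found 1 − Φ(0.411) = 34%

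AUROC stays at 0.75 throughout, so it gives no sign that the error-minimising cut-off flags almost nobody.

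**Step 5. Effect of the coding.** Swapping the positive and negative labels exchanges TP with TN and FP with FN. Total error, (FP + FN)/N, does not change, and neither does AUROC. Sensitivity and precision do change. The coding therefore affects what is reported and not which model wins on total error.

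**The case against.** Several counter-arguments stand, and they limit the point.

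- **The coding does not cause the selection problem.** A reader might infer that making completers positive lets a useless model win. Step 5 shows that it does not; the unweighted error rule does that.
- **AUROC is in Table 4.** A reader might infer that nothing in the plan could reveal a model that calls everyone a completer. AUROC would be 0.50, which the table itself treats as valueless. What remains is that no rule ranks AUROC above total error, and that AUROC does not reveal a model that ranks well but flags almost nobody (Step 4).
- **AUROC uses predicted scores.** It would be too strong to say that no listed metric uses probabilities. What is absent is a check of calibration, which an article may leave to a fuller plan.
- **The completion rate is unknown.** The document gives no sign that completion is above 80% or so. If non-completers were the large majority, the same rule would lean towards flagging everyone, which does not target either.
- **The operating point in Step 1 is fixed.** A real algorithm chosen on total error could move its cut-off, so Step 1 alone does not show that an informative algorithm loses. Step 4 covers that case: the cut-off moves, and few poor performers are found.
- **The coding is offered as an illustration and fits Objective 2a and the stated completion probability.** That is fair. Poor performance may also mean a low score. But no other coding is given for Objective 2b.

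A reader might also extend the point to Kilkari. The document gives no true or false positive coding there, and the loss categories and listening levels are not stated to be binary, so the extension is not supported.

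**Conclusion.** The point holds in a limited form. The stated selection rule, minimum unweighted total error followed by best fit and accuracy, is poorly matched to Objective 2b and can choose a model that finds few or no poor performers. With correctly computed error this requires completers to be a clear majority: above 82.4% for the 70%/85% comparator (100 − 17.6), and above about 78% to 88% for the others tried. For a model that ranks well, the error-minimising cut-off finds 3%, 16% and 34% of non-completers at 10%, 20% and 30% non-completion, under the binormal assumption with AUROC 0.75. All rates are assumed.

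Separately, the illustrated coding leaves recall and predictive value for the targeted group out of the listed metrics. The document does not show that a useless model will be selected, only that its rules do not prevent it. This is an inexpensive improvement worth making and not a flaw that invalidates the analysis.

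**What to change.** For Objective 2b:

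1. Code the non-completer, or the poor performer as the authors define it, as the positive class, so that sensitivity and precision in Table 4 describe the group to be targeted.
2. Replace minimum total error as the selection rule with the highest AUROC (already in Table 4) or the lowest Brier score on the test set. The Brier score also suits the stated wish for a probability of finishing. Changing the labels alone is not enough, because total error and AUROC are the same either way.
3. Report sensitivity and positive predictive value for poor performers at a fixed flagging rate chosen in advance.

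The cost is a change of wording and some reanalysis of data already to hand; no new data are needed. The reported total error may look slightly worse than under the present rule.

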**Unsupervised**				
	7 K-means	K-means clustering is a way to use data to uncover natural groupings within a heterogeneous population	Grouping of ASHA workers by user characteristics and patterns of training initiation and completion	User characteristics associated with exposure to messaging content and duration

Our choice of methods will include a mix of algorithms based on their strengths and weaknesses and the objective of the process. A comprehensive comparison of supervised learning methods is provided in literature [17,18]. SVM and NNs are expected to perform better with continuous data while the Naïve Bayes method and decision trees perform better with discrete/categorical variables. Naïve Bayes and decision trees have good tolerance to missing values, while NNs and SVM do not. NNs and Naïve Bayes have difficulty handling irrelevant and redundant attributes (ie, extra variables with no useful information or variables with too many categories and too few numbers), while SVM and decision trees are insensitive towards them. Variables with high correlation negatively affect the performance of both Naïve Bayes and NNs, whereas SVM are relatively robust to correlated variables. While Naïve Bayes is robust to noise, NNs are sensitive to poor measurement of variables and susceptible to overfitting. NNs and SVM perform well with multidimensional data and when there is a nonlinear relationship between predictor and outcome. Naïve Bayes requires less memory for both training and validation phase, whereas NN requires large memory allocation across all phases. SVM and NNs usually outperform other methods while Naïve Bayes may yield less accurate results. Table 3 compares the strengths and weakness of different supervised machine learning methods.

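### Mobile Academy predictions are meant to include each ASHA's probability of finishing, but none of the metrics that select and validate the models can show whether a probability is too extreme or too moderate

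*Protocol article*

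**What the plan says.** Three parts of the protocol article bear on this.

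- **Output.** The last paragraph of Testing and Validation states that "predictions for Mobile Academy will aim to determine the probability of the ASHA finishing the course in a predetermined time frame". The same sentence also names a possible score or performance level.
- **Selection rule.** Training of Algorithms says approaches will be "selected based on their ability to minimize the total error of the classification", and defines that error as "the probability that a solution will classify an object under the wrong category".
- **Metrics.** Testing and Validation says "Table 4 summarizes the four proposed metrics for assessing the performance of each model": accuracy, precision, sensitivity and AUROC. At Step 1, "Results from the performance metrics will help define the final model for each algorithm". After Step 2, "Using the same performance metrics, the models with the best fit and accuracy will be applied to the validation dataset as part of Step 3".

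Fit is mentioned once more at Step 1 ("The emerging results will then be assessed for model fit and accuracy"), but no measure of fit is named outside Table 4. The article mentions no calibration plot, calibration slope or intercept, Brier score or log loss.

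**The concern.** A probability and a class are different products and need different checks. A class is good if few people are misclassified. A probability is good if, among ASHAs given 90%, about 90% finish.

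The article names a probability as one thing it aims to deliver, then fixes a selection rule and four metrics that assess only classes and ranking. A model could pass Steps 1 to 3 with good results and still report probabilities far from the observed completion rates. Any later use of the absolute values, such as estimating how many ASHAs are likely to drop out, would then be wrong with no warning from the validation step.

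The candidate list makes this a practical matter:

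- A standard SVM produces a decision score and no probability. Table 3 gives it the top rating for general accuracy, so an accuracy-based rule may well select it.
- For two other candidates, the text after Table 2 warns that "Variables with high correlation negatively affect the performance of both Naïve Bayes and NNs". In Naïve Bayes, double-counting correlated predictors pushes probabilities towards 0 and 1.

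**Working it through.** The article gives no figure on this point, so there is nothing to reproduce. The check is one of logic, with illustrations on assumed inputs.

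**1. What the metrics can see.** Let p be the correct probability and let the model report q, where logit(q) = k × logit(p). With k > 1 the reports are too extreme, and with k < 1 too moderate.

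- q ≥ 0.5 exactly when p ≥ 0.5, so TP, FP, TN and FN are unchanged. Accuracy, precision and sensitivity are therefore unchanged, including accuracy by the formula as printed in Table 4.
- AUROC depends only on rank order, which is also unchanged.
- The expected Brier contribution is p(1 − q)² + (1 − p)q², and this does change. For log-odds of 1, p = 0.731. With k = 5, q = 0.993. The contribution rises from 0.731 × 0.269 = 0.197 to 0.731 × 0.007² + 0.269 × 0.993² = 0.265.

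**2. One-predictor illustration.** Assumed: logistic truth with log-odds x ~ N(0,1), n = 1,000,000, cut-off 0.5. The third decimal varies by about 0.001 between runs.

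| k | Accuracy | AUROC | Brier | Predicted above 90%: mean prediction | Same group: observed |
|---|---|---|---|---|---|
| 1 | 0.675 | 0.740 | 0.206 | – | – |
| 3 | 0.675 | 0.740 | 0.236 | 97% | 78% |
| 5 | 0.675 | 0.740 | 0.261 | 98% | 74% |

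Predicting 50% for everyone gives a Brier score of 0.250, so at k = 5 the probabilities do worse than that.

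**3. A different completion rate, and under-confidence.** Assumed: log-odds ~ N(−1, 1.2²), about 31% completing, n = 200,000.

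| k | Accuracy | Precision | Sensitivity | AUROC | Brier | Top decile: predicted / observed | Mean prediction (observed 0.313) |
|---|---|---|---|---|---|---|---|
| 1 | 0.747 | 0.650 | 0.417 | 0.773 | 0.171 | 0.74 / 0.74 | 0.313 |
| 3 | 0.747 | 0.650 | 0.417 | 0.773 | 0.197 | 0.94 / 0.74 | 0.226 |
| 0.33 | 0.747 | 0.650 | 0.417 | 0.773 | 0.197 | 0.59 / 0.74 | 0.421 |

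All four metrics are identical across rows, and the probabilities are not. At about 50% and 69% completion the four metrics are likewise unchanged by k, while the Brier score changes.

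**4. Where the metrics do react.** The invariance needs both ranking and cut-off to be preserved.

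- Two independent N(0,1) predictors with coefficient 1 each, one counted five times: AUROC falls from 0.803 to 0.748 and accuracy from 0.725 to 0.681.
- Four such predictors, one counted five times: AUROC falls from 0.862 to 0.767 and accuracy from 0.778 to 0.696.
- In the one-predictor model, adding 1 to every log-odds moves accuracy from 0.675 to 0.600 and sensitivity from 0.674 to 0.941.

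The blind spot is therefore a distortion that keeps the order and the cut-off.

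**The case against.** **The task is mainly classification.** Objective 2b asks for a classifier, the Algorithms section describes the analyses as classification, Table 2 lists the supervised Mobile Academy uses as classification, and the Conclusions speak of developing classifiers. For that work the Table 4 metrics are suitable. This stands, and it limits the point to the probability output. It does not remove the point, because that output is stated separately.

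**The harm is inferred.** A reader might conclude that the programme will target ASHAs by predicted probability or around an action threshold. The article does not say so. It describes identifying groups and likely poor performers. Under a distortion that keeps ranking and cut-off, the same ASHAs would be flagged.

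**The plan acts against the cause.** A reader might infer that Naïve Bayes will produce badly inflated probabilities here. The Processing section plans to reduce correlated and collinear variables, the Algorithms section allows principal components, and Table 3 gives Naïve Bayes the lowest rating for general accuracy, so it is the candidate least expected to win. This stands, although it supplies no probability for an SVM.

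**The metrics are not wholly blind.** A reader might conclude that AUROC can never reveal the failure. Step 4 of the working shows otherwise when the ranking or the intercept shifts.

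**It is an omission that a fuller plan may fill.** Calibration reporting is often left to an analysis plan, and the metrics are said only to help define the final model. That would answer a silent article. This one names the output, the selection criterion and the four metrics, and carries the same metrics into the choice for validation. The mismatch is therefore in what is written. How SVM scores are mapped to probabilities could fairly be left to a fuller document.

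**Conclusion.** The point holds in a limited form. The article aims to deliver a probability of finishing, but its stated selection and validation measures cannot detect probabilities that are too extreme or too moderate when ranking and cut-off are preserved. In the illustrations, every Table 4 metric stayed the same while predicted and observed completion differed by 24 percentage points (98% against 74% above the 90% prediction, k = 5) or by 20 and 15 points in the top decile (k = 3 and k = 0.33).

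These sizes rest on assumed distributions, completion rates and values of k, none of which comes from the article. They show that a miscalibrated model can pass unnoticed, not that one will. The classifier objective is unaffected. The change is worth making because it is cheap and settles what the probability output means.

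**What to change.** - Keep the four Table 4 metrics for the classifier in Objective 2b.
- For any output reported as a probability, add the Brier score or log loss to Table 4 and consider it alongside the existing metrics at Step 2. Making it the sole selector would be debatable, given the classifier objective.
- Where the check shows a need, recalibrate on data outside the validation set (for example by Platt scaling or isotonic regression). If an SVM is used for this output, map its scores to probabilities on those data too.
- At Step 3, report calibration slope, intercept and plot on the untouched validation set.
- Alternatively, if no probability will be used, restate the Mobile Academy output as a class only and drop the reference to a probability.

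The cost is slightly more analysis code, one more table row and a plot, with no new data. The downside is that a model with marginally lower accuracy may be preferred for the probability output.
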